### Interim safety analyses {21b}

The DSMB will conduct three interim safety analyses throughout the trial to assess in-hospital mortality after 240 (20%), 400 (33%), and 800 (66%) infants recruited.

### Methods for additional analyses (e.g., subgroup analyses) {20b}

For the primary outcome, the following subgroups will be analyzed: (i) gestational age 23^+0^–25^+6^ vs. 26^+0^–28^+6^; (ii) infants supported with CPAP vs. received mask ventilation [52]; (iii) female vs. male [53, 54].

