**Methods:**

An international cluster, cross-over randomized trial of initial FiO_2_ of 0.3 or 0.6 during neonatal resuscitation in preterm infants at birth to increase survival free of major neurodevelopmental outcomes at 18 and 24 months corrected age will be conducted. Preterm infants born between 23^0/7^ and 28^6/7^ weeks’ gestation will be eligible. Each participating hospital will be randomized to either an initial FiO_2_ concentration of either 0.3 or 0.6 to recruit for up to 12 months’ and then crossed over to the other concentration for up to 12 months. The intervention will be initial FiO_2_ of 0.6, and the comparator will be initial FiO_2_ of 0.3 during respiratory support in the delivery room. The sample size will be 1200 preterm infants. This will yield 80% power, assuming a type 1 error of 5% to detect a 25% reduction in relative risk of the primary outcome from 35 to 26.5%. The primary outcome will be a composite of all-cause mortality or the presence of a major neurodevelopmental outcome between 18 and 24 months corrected age. Secondary outcomes will include the components of the primary outcome (death, cerebral palsy, major developmental delay involving cognition, speech, visual, or hearing impairment) in addition to neonatal morbidities (severe brain injury, bronchopulmonary dysplasia; and severe retinopathy of prematurity).

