In a non-pre-specified analysis of the Targeted Oxygen in the Resuscitation of Preterm Infants Trial, infants of < 28 weeks’ gestation who received an initial FiO_2_ of 0.21 at resuscitation had higher hospital mortality than those given an initial FiO_2_ of 1.0 (10/46 [22%] vs. 3/54 [6%]; RR: 3.9 [95% CI: 1.1–13.4]; *p* = 0.01) [23]. Furthermore, the most recent individual patient analysis of eight trials reported that infants who were started with an initial FiO_2_ of < 0.3 had significantly lower 5 min SpO_2_ values compared to infants started with an initial FiO_2_ of ≥ 0.6 [35]. Furthermore, infants initially resuscitated with initial FiO_2_ of 0.21–0.3 compared to initial FiO_2_ of ≥ 0.6 had an increased risk of major intraventricular hemorrhage and a five times higher risk of death [35]. Similarly, if preterm infants resuscitated with initial low FiO_2_ do not reach SpO_2_ of 80% at 5 min, it was associated with increased risk of major intraventricular hemorrhage and an almost five times higher risk of death [35]. There is equally growing evidence that using lower initial FiO_2_ will lead to lower SpO_2_ levels and bradycardia, which may lead to increased rates of mortality in this vulnerable group of infants [34, 36]. These data provide a warning note for the use of higher vs. lower initial FiO_2_ during delivery room resuscitation. Trials are urgently needed to evaluate the risk of using low and high initial FiO_2_ in preterm infant stabilization at birth [37]. In summary, the “optimal” FiO_2_ used to initiate post birth stabilization of extreme preterm seems to be about balancing the need to quickly achieve target saturations while minimizing the oxidative stress of “too much” oxygen.

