#### ***Initial FiO***_***2***_*** of 0.6 arm***

Infants randomized to this arm will receive initial FiO_2_ of 0.6 during the first 3 min of life. Focus will be on providing effective ventilation. During this time, if SpO_2_ is available and reliable, oxygen may be increased by 20% every minute if an SpO_2_ ≥ 85% is unlikely to be achieved by 5 min. Once a reliable SpO_2_ reading is available, or at the latest at 3 min of age, the clinical team will assess SpO_2_. If SpO_2_ is < 85%, oxygen should be increased by 20% every 60 s to achieve SpO_2_ ≥ 85% at 5 min of age. If SpO_2_ is > 95% at or before 5 min of age, oxygen should be decreased by 10–20% every 60 s to maintain SpO_2_ of ≥ 85%. At 10 min of age and beyond, aim for SpO_2_ of 90–95% or as per institutional guidelines. If, at any time during the resuscitation, the HR is 60–100 and not increasing with effective ventilation, oxygen will be increased by 20% every min, regardless of SpO_2_ (Fig. 1).

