### Duration of treatment period

The study intervention duration will be the first 10 min after birth.

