### Sample size {14}

A sample size of 1200 (600 per group, adjusted for 10% loss of follow-up) infants has been determined based on: baseline outcome rate of 35% (18% mortality and 17% abnormal neurodevelopmental outcomes) [48], RRR of 25%, type I error of 5%, power of 80%, within-cluster within-period ICC of 0.034, within-cluster between-period ICC of 0.029, cluster size in each arm of 10–80 (unequal cluster period but equal cluster size), and loss to follow-up rate of ~ 10%. ICCs were derived from existing data from the Canadian Neonatal Network sites [48]. With these assumptions, we will need up to 20 centers (clusters) to recruit 20–80 patients per arm (20–160/center) for a total of 1200 neonates at all sites.

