### Implementation {16c}

Before the start of the trial, the statistician will use computer-generated random numbers to prepare the allocation sequence for all participating centers by producing the codes and allocation table, which then will be validated by an independent statistician. Clinical staff attending neonatal deliveries know the group assignment and will enroll every participant automatically, as the group assignment is also local hospital policy.

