## Statistical methods

### Statistical methods for primary and secondary outcomes {20a}

A detailed statistical analysis plan will be finalized and submitted for publication prior to database lock. Data handling, verification, and analysis for the HiLo trial will be performed by WCHRI. Statistical analysis will follow standard methods for randomized trials, and reporting of findings will be performed in accordance with CONSORT guidelines extension for cluster trials [51].

The primary analysis will be conducted using an “intention-to-treat” approach. For the primary outcome, generalized linear mixed model with binary outcome and maximum likelihood estimate will be used to evaluate the effect of an oxygen concentration on the primary outcome. To account for cluster crossover design of the study, effects of centers (clusters) and a period (oxygen concentration) within center will be considered random, and effects of the intervention (oxygen concentration) will be entered as a fixed effect. This hierarchical model allows for the correlation of patients within periods and within clusters. The model will be adjusted for gestational age and if the infant required mask ventilation as potential confounding variables. To account for multiple births when more than one infant is enrolled in the study, clustering within mothers will be entered as a random effect in the model and this model will be tested for a better fit.

Similar generalized linear mixed models will be performed to evaluate the effect of group on secondary outcomes. If convergence problems arise, different fitting techniques will be used depending on the nature of the problem. For example, different approximation methods (e.g., maximum likelihood or pseudo-likelihood methods) will be tried; different types of covariance structures will be used. In addition, in case of singularity of variance–covariance matrix, models with fewer random effects will be created if the fit is adequate.

Analysis of secondary outcomes will use generalized linear mixed models or descriptive analysis. Summary statistics will be presented for baseline and clinical characteristics: continuous data by mean, two-sided 95% CI of the mean, standard deviation, median, interquartile range (first and third quartiles), minimum and maximum. Categorical data will be presented by absolute and relative frequencies.

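### The CPAP versus mask-ventilation subgroup is formed after allocation, so its within-stratum effects are not randomised comparisons if initial FiO2 changes who is ventilated

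*Protocol article*

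**What the plan says.** The section on additional analyses {20b} names three subgroups for the primary outcome: gestational age band, sex, and "infants supported with CPAP vs. received mask ventilation". The support split has no time point, does not say whether it means the first mode of support or any mask ventilation, and carries no caution. It stands level with the two baseline factors.

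Other sections of the protocol article place that variable in time:

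- **Start of exposure.** Under the 0.6 arm: "Infants randomized to this arm will receive initial FiO_2_ of 0.6 during the first 3 min of life". The 0.3 arm has parallel wording.
- **Length of exposure.** "The study intervention duration will be the first 10 min after birth".
- **Awareness of the arm.** Implementation {16c}: "Clinical staff attending neonatal deliveries know the group assignment".
- **Expected physiology.** The evidence summary expects that "using lower initial FiO_2_ will lead to lower SpO_2_ levels and bradycardia".
- **Outcome list.** The secondary outcomes include the proportions of infants breathing on their own or being mask-ventilated at minutes 3 and 5.

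**The concern.** A subgroup analysis keeps the protection of randomisation only if the factor could not have been affected by the allocated arm. Gestational age and sex meet that test. Mode of support does not, because CPAP or mask ventilation is given while the allocated oxygen is running.

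Suppose 0.6 spares some borderline infants from mask ventilation. The CPAP stratum of the 0.6 arm then gains infants who are sicker than its usual members, and the ventilated stratum of that arm keeps only the sickest. Both strata look worse under 0.6 although no infant was harmed. If 0.6 instead led to more mask ventilation, the distortion would run the other way.

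At stake is the reading of one of only three named subgroups for the primary outcome. A difference or similarity between strata could be taken for evidence about which infants benefit when it reflects only who ended up in which stratum.

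**Working it through.** **The plan's own figures.** The plan gives no figure for this subgroup: no mask-ventilation rate and no risk by support mode. The one usable anchor is the "baseline outcome rate of 35% (18% mortality and 17% abnormal neurodevelopmental outcomes") in the sample size section: 18% + 17% = 35%. The inputs below are assumed and chosen to return that 35%.

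**Assumed inputs, 0.3 arm.** Ventilated share V = 0.75 with risk 0.40; CPAP share C = 0.25 with risk 0.20. Overall: 0.75 × 0.40 + 0.25 × 0.20 = 0.30 + 0.05 = 0.35.

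**Assumed effect of 0.6.** It moves a share s of all infants, with risk 0.30, from ventilation to CPAP, and changes no infant's outcome.

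- Ventilated risk in the 0.6 arm = (0.30 − s × 0.30) / (0.75 − s)
- CPAP risk in the 0.6 arm = (0.05 + s × 0.30) / (0.25 + s)

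| Shift s | Ventilated, 0.6 arm | Apparent harm (vs 40%) | CPAP, 0.6 arm | Apparent harm (vs 20%) | Overall, 0.6 arm |
|---|---|---|---|---|---|
| 0 | 0.300/0.75 = 40.0% | 0 | 0.050/0.25 = 20.0% | 0 | 35% |
| 0.05 | 0.285/0.70 = 40.7% | 0.7 points | 0.065/0.30 = 21.7% | 1.7 points | 0.285 + 0.065 = 35% |
| 0.10 | 0.270/0.65 = 41.5% | 1.5 points | 0.080/0.35 = 22.9% | 2.9 points | 0.270 + 0.080 = 35% |
| 0.15 | 0.255/0.60 = 42.5% | 2.5 points | 0.095/0.40 = 23.75% | 3.75 points | 0.255 + 0.095 = 35% |

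The distortion has the same sign in both strata because the moved infants' risk (30%) lies between the two stratum risks (20% and 40%).

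**A second set of assumed inputs.** Ventilated share 50% or 70% under 0.3; shift 5% to 15% of all infants; risks in the ratio 0.20:0.35:0.45 or 0.25:0.35:0.40 for always CPAP, moved, and always ventilated; all scaled to 35% overall. One case in full, with 70% ventilated, a 15% shift and the first ratio:

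- Scaling: 0.30 × 0.20 + 0.15 × 0.35 + 0.55 × 0.45 = 0.36, so the factor is 0.35/0.36 and the risks are 0.194, 0.340 and 0.438.
- CPAP: 0.194 under 0.3; (0.30 × 0.194 + 0.15 × 0.340)/0.45 = 0.243 under 0.6; risk ratio 1.25.
- Ventilated: (0.15 × 0.340 + 0.55 × 0.438)/0.70 = 0.417 under 0.3; 0.438 under 0.6; risk ratio 1.05.

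Over the whole grid, with no true effect, the spurious risk ratio (0.6 versus 0.3) is 1.04 to 1.25 in the CPAP stratum and 1.01 to 1.07 in the ventilated stratum, while the overall ratio stays at 1.00. With a true risk ratio of 0.75 in every infant (the planned 25% reduction) and the first risk ratio set, the strata show 0.80 to 0.94 (CPAP) and 0.76 to 0.80 (ventilated). A zero shift gives no bias in any of these settings.

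**The case against.** **Timing.** The subgroup section sets no time point. If it means the first mode of support, chosen almost as the gas is turned on, the oxygen itself has little chance to alter it. That would make the bias small, but it does not make the factor a baseline one. Each hospital's arm is its policy before the birth, and the staff who choose the support know it, so even the first mode is a post-allocation, unblinded choice.

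**Mechanism.** Both arm descriptions respond to low saturation, and to a heart rate of 60–100 that is not rising, by giving more oxygen. The expected bradycardia therefore need not change the mode of ventilation. This stands: no figure in the documents shows a shift.

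**Size.** The inputs are assumed, and a 15-point shift is the top of the range shown. With 600 per arm, ignoring clustering and loss, the standard errors of the subgroup differences at that shift are √(0.40 × 0.60/450 + 0.425 × 0.575/360) ≈ 3.5 points (ventilated) and √(0.20 × 0.80/150 + 0.2375 × 0.7625/240) ≈ 4.3 points (CPAP). Both biases are below one standard error. This also stands, though more infants would not remove a bias.

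**Left to the analysis plan.** Interaction tests and an exploratory label may properly come later. The choice of factor, however, is stated here, and a later plan would have to reverse or qualify it.

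**Stronger readings to avoid.** A reader might infer that the subgroup certainly compares different kinds of infants, or is uninterpretable. The documents support only the conditional statement. A reader might also infer that the subgroup factor is itself a listed outcome. The secondary outcome contrasts spontaneous breathing with mask ventilation at two set times, whereas the subgroup contrasts CPAP with mask ventilation at no set time. They are closely related but not shown to be the same.

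**Conclusion.** The point holds in conditional form. The plan commits to a primary-outcome subgroup on a status set after allocation, during exposure, by unblinded staff. If initial FiO2 changes who is mask-ventilated, the within-stratum contrasts are not randomised and can mislead in the same direction in both strata; if it does not, this bias is absent. On the assumed inputs, a 5 to 15 point shift yields about 0.7 to 2.5 points of false harm in the ventilated stratum and 1.7 to 3.75 points in the CPAP stratum, with no overall difference. The ventilation share, stratum risks and shift are all assumptions; only the 35% overall rate is the protocol's.

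The consequence is confined to one secondary table. The primary model uses a similar variable ("The model will be adjusted for gestational age and if the infant required mask ventilation as potential confounding variables"), which is a separate matter, not settled by this point.

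**What to change.** Remove the CPAP versus mask-ventilation split from the effect-modification subgroups, keep gestational age and sex, and report support mode by arm as an outcome; the existing secondary outcome at 3 and 5 minutes already does much of this. If the split is kept, label it exploratory and non-randomised, and fix its definition and time point in the protocol or the analysis plan.

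A severity subgroup built only from pre-birth data is optional. The participant timeline already lists maternal and pregnancy data, but this would need a specified prediction model and would overlap with the gestational age and sex subgroups.

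The cost is wording, plus one planned table lost or downgraded. Statistical methods {20a} has the analysis plan finalised before database lock, and Trial status expects recruitment to end in early to mid-2026 and results in late 2028, so the change can be made in that plan before lock.

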### Analysis population and missing data {20c}

A sensitivity analysis will be performed to examine the effect of missing values in primary and secondary outcome variables. Multiple imputation will be used for missing data; a very low number of missing values are expected due to study design. To mitigate the problem of higher-than-expected rate of missing values for the primary outcome, the HiLo trial will publish the results of in-hospital mortality (secondary outcome) and severe brain injury on cranial ultrasound (secondary outcome) before the primary composite outcome of all-cause mortality or the presence of a major neurodevelopmental outcome. This will assure a close to 100% ascertainment and prevent the HiLo trial from falling below 100% of achieved sample size, to avoid that trial results become progressively more fragile, and a random or non-random imbalance in the primary outcome among participants with missing values could erase an apparently statistically significant result [41–43].

### Plans to give access to the full protocol, participant level-data and statistical code {31c}

There is full public access to clinical trial registration (NCT03825835; www.clinicaltrials.gov); information is at the Hilo trial website (https://www.hilotrial.org and https://www.research4babies.org/hilo). This study protocol and the statistical analysis plan will be available and submitted for publication.

The complete de-identified HiLo trial dataset collected for this analysis will be available 6 months after publication of the primary outcome. The HiLo trial dataset will be also integrated into the prospective PROspective Meta-analysis Of Trials of Initial Oxygen in preterm Newborns (PROMOTION) [55] and an updated version of the retrospective NETwork Meta-analysis Of Trials of Initial Oxygen in preterm Newborns (NETMOTION) [56]. This study protocol and the statistical analysis plan will also be available and will have been submitted for publication in a journal. An application to obtain the data may be made by emailing [contact]. The final decision to share data will be made by the HiLo trial steering committee.

## Oversight and monitoring

### Composition of the coordinating center and trial steering committee {5d}

The trial management team is based at the Royal Alexandra Hospital, Edmonton, Canada, which includes the principal investigators ([name]) and the trial coordinators ([name] and [name]) and meets weekly. [name] is the executive director of the Canadian Premature Babies Foundation and has been involved in the trial design.

### Trial steering committee

The trial steering committee detailed below meets approximately quarterly, chaired by [name].

### Composition of the data monitoring committee, its role, and reporting structure {21a}

The data and safety monitoring board (DSMB) has three independent members (chair, a neonatal clinician, and a biostatistician). The role of the DSMB was outlined in a DSMB Charter finalized prior to the trial commencing. DSMB is responsible to protect and safeguard the interests of all study patients, monitor the overall conduct of the trial, advise the investigators to protect the integrity of the trial, and supervise the conduct and analysis of all interim analyses. The DSMB detailed below meets approximately every 6 months as well as for each interim safety analyses, chaired by [name].

### Adverse event reporting and harms {22}

Safety reporting from the HiLo trial will follow standards from Health Canada as per section C.05.014 of the Food and Drug Regulations and the Tri-Council Policy Statement: Ethical Conduct for Research Involving Humans [38].

Pre-defined SAE are as follows:Death in the delivery room (also a component of the primary outcome)Death in the NICU (also a component of the primary outcome)Intraventricular hemorrhage grade 3 or higher according to Papile [44]

### Auditing {23}

The Quality Management in Clinical Research (QMCR), University of Alberta, will act as an independent monitor and will perform virtual site data auditing every 3 months to review source documentation. As this trial was classified as regulatory trial according to Health Canada regulations, auditors with Health Canada might also audit the data for adherence.

The ethics committee will meet annually to review conduct, the independent DSMB meets every 6 months to review conduct of study as well as for every interim safety analysis, and the trial steering committee will meet quarterly to review conduct throughout the trial period.

### Plans for communicating important protocol amendments to relevant parties {25}

There have not been any major changes to the trial protocol since the trial began. Minor changes and additions have been submitted for approval to the Health Research Ethics Board (Edmonton, Canada), Health Canada, and all other relevant ethics committees and distributed and communicated to each participating site.

## Dissemination plans

### Trial results {31a}

The results of the trial will be presented at national and international conferences and published in high-impact medical journals. Media and social media opportunities will be sought to communicate the results to the public. We will collaborate with the Canadian Premature Babies Foundation to create lay summary for distribution to all participating families.

## Discussion

Using an initial FiO_2_ of 0.6 may decrease major neurodevelopmental outcomes and improve health benefits in children. The international, cluster randomized HiLo trial is powered to allow the detection of an important difference in the primary outcome of survival free of major neurodevelopmental outcomes at 18–24 months corrected age. The HiLo trial will address gaps in the evidence for the initial oxygen concentration due to its pragmatic and inclusive design, including all extremely preterm infants. Assessment of surviving infants at 18–24 months corrected age (corrected for prematurity) will provide evidence of longer-term efficacy and safety, which is critical for trials in extremely preterm infants.

## Trial status

The current protocol version is 3.5, dated October 4, 2022. Recruitment began in June 2022 at Royal Alexandra Hospital, Edmonton, with additional sites added over time. Recruitment is expected to be completed in early to mid-2026 with results expected in late 2028.

## Data Availability

The complete de-identified HiLo trial dataset collected for this analysis will be available 6 months after publication of the primary outcome. The HiLo trial dataset will be also integrated into the prospective PROspective Meta-analysis Of Trials of Initial Oxygen in preterm Newborns (PROMOTION) [55] and an updated version of the retrospective NETwork Meta-analysis Of Trials of Initial Oxygen in preterm Newborns (NETMOTION) [56]. This study protocol and the statistical analysis plan will also be available and will have been submitted for publication in a journal. An application to obtain the data may be made by emailing [contact]. The final decision to share data will be made by the HiLo trial steering committee.

